**Methods:**

A total of 40 patients requiring outpatient laser therapy for at least 2 sessions will be recruited from a pediatric hospital in the Midwestern United States for this crossover randomized, 2-arm clinical trial. During the first laser visit, the participants will be randomly assigned to either play the VR-PAT game during their procedure or wear the headset with a dark screen. Participants will answer questions about their pain (Numeric Rating Scale 0‐10), anxiety (State-Trait Anxiety Inventory for Children, Numeric Rating Scale 0‐10, and Modified Yale Preoperative Anxiety Scale), and pain medication usage. Those playing the VR-PAT will report simulator sickness symptoms and their experience playing the game. At their second laser visit, participants will cross over to the opposite intervention. The primary outcomes are the differences in self-reported pain and anxiety between the 2 interventions. Feasibility outcomes include the proportion of screened patients who were eligible, have given consent, and completed both visits, as well as adverse events reported. To evaluate the efficacy of pain reduction, composite pain scores, and pain medication usage will be calculated for each laser visit. To evaluate the efficacy of anxiety reduction, the change in Modified Yale Preoperative Anxiety Scale scores will be compared between control and VR groups at each visit using the Wilcoxon rank sum tests. All statistical analyses will follow the intention-to-treat principle with regard to intervention assignment at each visit.

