### Participant Timeline

Study enrollment at NCH—patients will be recruited prior to their first sequential dermatologic laser procedure. After consent and assent (if applicable) are obtained, patients will be randomized to either the VR-PAT intervention or the control group. A research associate will collect background information, such as demographics, anxiety levels, and prior video game experience, before randomization. VR-PAT instructions will be provided to the intervention group prior to participation.

Laser procedures at NCH (n=2 visits)—patients will receive their laser procedure as usual. Participants in the intervention group will wear the Pico headset and play the VR-PAT during their procedure. Participants in the control group will receive their laser procedure while wearing the VR headset (without the game). A researcher in the laser treatment room will observe the procedure and document, for the intervention group, the amount of time spent playing the VR-PAT, whether the participant declined to use it, and the number of interruptions of VR. Following the procedure, a different researcher (blinded to the group) will ask both groups of participants about their pain experience and satisfaction with the game. This process will be repeated once for each participant, as they will cross-over to the opposite intervention group at their next laser procedure.

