#### Observed Measures (Research Collected)

The Modified Yale Preoperative Anxiety Scale (mYPAS) [37] will be assessed at each laser procedure before entering the treatment room, before the procedure begins, and immediately following the procedure. This is a 5-item scale, with a score of more than 30 indicating anxiety. During the procedure, the researcher will document the start and stop times of the laser procedure, the start and stop times of the VR (if applicable), whether the participant declined to use the VR-PAT, and the number of voluntary interruptions of the VR-PAT.

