#### Primary Outcomes

Difference in self-reported worst pain, average pain, and time spent thinking about pain (NRS 0 [min]−10 [max]) between VR-PAT and control visits. These questions are asked at each visit and will be compared between the intervention and control visits.

Change in procedural anxiety (mYPAS observed by the researcher, 23.33 [min]−100 [max], with higher scores denoting higher levels of anxiety) is assessed at 3 time points: prior to entering the procedure room, prior to the procedure, and immediately following the procedure for each laser procedure. These differences will be compared before and after the procedure, as well as between the intervention and control visits.

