For aim 2, the mYPAS score had 6 repeated measurements over time (T0, T1, and T2 during each of the 2 laser procedures). At the first procedure, we will compare the change in mYPAS scores from T0 to T1 and T0 to T2 between the control and VR groups using either 2-sample 1-tailed *t* tests or the Wilcoxon rank sum tests (depending on the distribution of the change in mYPAS scores). The clinical effect size will be the difference in medians of the change in mYPAS, with the confidence limits calculated by bootstrapping with replacement using 1000 repetitions. Bootstrapping has been found to provide better confidence limits with asymmetric data, such as the mYPAS score in our study, and is the recommended method. The same statistical analysis approach has been successfully used by other researchers, who reported that VR effectively reduced preoperative anxiety among 71 children aged 5 to 12 years scheduled for elective surgery [42]. At the second procedure, we will compare the mYPAS scores at T0 and T1 between the control and VR groups using the Wilcoxon rank sum tests since mYPAS scores are shown to be asymmetric [42]. The clinical effect size will be the difference in medians of mYPAS. Confidence limits will be calculated using bootstrapping again.

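### At visit 2 the planned mYPAS comparison uses only pre-procedure scores, so it cannot estimate the effect of VR during that procedure and conflicts with the stated primary outcome

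*Protocol article*

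**What the plan says.** **Timing of the scores.** Observed Measures places the three mYPAS assessments "before entering the treatment room, before the procedure begins, and immediately following the procedure", and Primary Outcomes gives the same order: "prior to entering the procedure room, prior to the procedure, and immediately following the procedure for each laser procedure". These are T0, T1 and T2.

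**Timing of VR.** Participant Timeline says that intervention participants "will wear the Pico headset and play the VR-PAT during their procedure".

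**Data collected.** Data Analysis states that "the mYPAS score had 6 repeated measurements over time (T0, T1, and T2 during each of the 2 laser procedures", so T2 exists at both visits.

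**Analysis at visit 1.** According to Data Analysis, "we will compare the change in mYPAS scores from T0 to T1 and T0 to T2 between the control and VR groups".

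**Analysis at visit 2.** The same section then says: "At the second procedure, we will compare the mYPAS scores at T0 and T1 between the control and VR groups". It uses raw scores in a rank sum test and calls the difference in medians the clinical effect size. It mentions neither T2 nor a change score.

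**The outcome as defined elsewhere.** Primary Outcomes asks for differences from before to after the procedure, and between VR and control visits. The Abstract says that the change in "Modified Yale Preoperative Anxiety Scale scores will be compared between control and VR groups at each visit", and that participants are grouped by their assignment at each visit.

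**The concern.** The visit-2 comparison is described as a clinical effect size for a primary outcome. Both of its scores come before the exposure they are meant to evaluate, and the one score that follows the exposure has no visit-2 analysis in Data Analysis.

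The crossover makes this worse. At visit 2 the participants labelled VR are those who had the dark headset at visit 1, and those labelled control have already had VR. The article itself gives reasons to expect carryover into later anticipatory anxiety. Background and Significance says that distress at one session can raise anxiety at later ones, and Gap in Knowledge says that VR reduces the formation of phobic responses to hospitals. A lasting benefit of visit-1 VR would therefore be credited to the visit-2 control group.

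The Sample Size section gives the purpose of this pilot as estimating effect sizes and variances for a larger trial. An estimate that is null by construction, or has the wrong sign, would mislead that planning.

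**Working it through.** The documents give no SD, effect size or power for mYPAS, so there is no planned figure to reproduce. The check has three parts.

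**1. Order of events at visit 2** (Observed Measures, Primary Outcomes, Participant Timeline)

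T0 → T1 → procedure with VR or dark headset → T2. Data Analysis uses T0 and T1. Primary Outcomes and the Abstract need a score taken after the procedure. The three statements cannot all describe the same analysis.

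**2. Direction of the contrast** (needs no numerical assumption)

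Let *m* be the mean visit-2 score without carryover or VR, *d* the reduction in T2 from VR at that visit, *c* the lasting reduction in visit-2 T0 from visit-1 VR, and *c₂* the same for visit-2 T2.

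| Sequence | Label at visit 2 | T0 | T2 |
|---|---|---|---|
| control, then VR | VR | *m* | *m* − *d* |
| VR, then control | control | *m* − *c* | *m* − *c₂* |

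VR minus control at visit 2 (negative favours VR):
- Planned contrast at T0: *m* − (*m* − *c*) = +*c*. It does not contain *d*.
- Raw T2: −*d* + *c₂*.
- T0-to-T2 change: −*d* − (*c* − *c₂*).

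Example with an assumed *c* = 5: the planned T0 contrast is +5, so VR looks 5 points worse although VR helped.

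Neither alternative is free of carryover. With *d* = 0 and *c* = 5:
- If *c₂* = 0, the change contrast is −(5 − 0) = −5, which favours VR with no direct effect. Raw T2 gives 0.
- If *c₂* = 5, the change contrast is 0. Raw T2 gives +5.

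For 0 ≤ *c₂* ≤ *c*, the two contrasts bracket −*d*. In a balanced two-period crossover with a period term, the estimate is the mean of the two visit contrasts. The visit-1 contrast has no carryover, so the bias is halved: −5 becomes (0 − 5)/2 = −2.5, and +5 becomes +2.5.

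**3. Illustrative operating characteristics**

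From the documents: 40 participants allocated 1:1, so about 20 per group; score range 23.33 to 100; Wilcoxon rank sum test. Assumed: mean 45, SD 15, correlation 0.6 between time points, one-sided 0.05 in each direction, and equal carryover on all visit-2 scores (*c* = *c₂*). There were 4,000 simulated trials per setting.

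| Setting | Planned T0 or T1 test | Raw T2 | T0-to-T2 change |
|---|---|---|---|
| *d* = 0, no carryover | favours VR in about 5% | about 5% | about 5% |
| *d* = 10, no carryover | about 5% | 63% | 66% |
| *d* = 15, no carryover | about 5% | 91% | 91% |
| *d* = 10, carryover 5 | favours VR in under 1%; VR significantly worse in 26% | 26% favour VR | 70% favour VR |
| *d* = 10, carryover 10 | favours VR in 0%; VR significantly worse in about 63% | 5% favour VR | 72% favour VR |

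The good showing of the change score in the last two rows depends on equal carryover, which cancels. Part 2 shows that it would not cancel if T0 alone were affected.

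**The case against.** **The visit-2 test may be meant for anticipation or carryover.** Objectives treats anxiety as a factor before the procedure. Visit-2 T0 follows the first exposure, so it is no longer a clean baseline, which could explain the use of raw scores. This stands in part: a reader might infer that the test can show no VR effect at all, and that goes too far. It could pick up expectation of VR or the after-effect of visit 1. But the article does not give it that purpose for mYPAS. Its only stated carryover test concerns the composite pain scores.

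**The sign depends on the label.** Randomization is to sequences, and Data Analysis speaks of assigned study groups without saying which visit defines them. If the visit-1 condition were the label, the sign would be as expected. The Abstract's statement on assignment at each visit points to the current condition.

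**T2 may not be discarded.** A reader might infer a settled decision to ignore 40 visit-2 T2 scores. The documents do not support that, because Primary Outcomes and the Abstract both imply that these scores are used. Data Analysis is the outlier.

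**T1 may not precede all exposure.** The article does not say whether the headset is already on at T1. If it is, T1 could carry some early effect. T0 could not, and neither score covers the procedure itself.

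**Switching to change scores is not a complete cure.** This stands, as part 2 of the working shows, and the fix allows for it.

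**Conclusion.** The point holds as an internal contradiction about a primary outcome, together with a stated visit-2 analysis that cannot estimate the effect of VR during that procedure. This follows from the order of events and needs no assumed numbers, with the one reservation about headset use at T1.

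The reversal of sign is conditional. It requires labelling by current assignment, which the Abstract supports, and some lasting benefit of visit-1 VR, which the article makes plausible but does not quantify. The 5- and 10-point carryovers, the SD of 15 and the resulting percentages are illustrations only.

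A reader might infer that the anxiety aim as a whole is lost. It is not: the randomized visit-1 T0-to-T2 comparison is intact, and the aim 1 pain comparison does not use this test. What is at risk is the second half of the post-procedure mYPAS data (40 of 80 scores among the 40 completers) and the within-participant comparison that the crossover was chosen to provide.

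**What to change.** Reconcile the Abstract, Primary Outcomes and Data Analysis:

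1. At visit 2, analyse the T0-to-T2 change, as at visit 1.
2. Estimate the VR-versus-control difference within participants across both visits, with a period term.
3. Because visit-2 T0 may carry over from visit 1, report as sensitivity analyses raw T2 (or T2 adjusted for visit-1 T0) and the visit-1-only estimate. Under the carryover pattern in the working, the change score and raw T2 err in opposite directions, so agreement between them is reassuring.
4. Keep any visit-2 T0/T1 comparison as an exploratory carryover or anticipation analysis, labelled by the visit-1 condition and not presented as the clinical effect size.

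The cost is a change of wording and slightly more analysis work. No new data are needed, since T2 is taken at both visits. The article reports data collection as complete and analysis as in progress, with the biostatistician blinded until the primary outcome analysis is done. The change should be dated and documented before that unblinding.

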### Settings and Participants

Participants will be enrolled from the outpatient dermatology clinic on the main campus of Nationwide Children’s Hospital (NCH) in Columbus, Ohio. We plan to recruit 40 patients (aged ≥5 y) to complete 2 laser visits who clinically require laser therapy. The inclusion criteria are: (1) dermatology patients (≥5 y) undergoing the first of a new series of laser procedures at the NCH Outpatient Dermatology Clinic, (2) having a legal guardian present for patients aged less than 18 years during the procedure (for informed consent), and (3) the ability to communicate orally. Exclusion criteria include: (1) any wounds that may interfere with study procedures; (2) use of the diode laser; (3) vision, hearing, or cognitive and motor impairments preventing valid administration of study measures; (4) history of motion sickness, seizure disorder, dizziness, or migraine headaches precipitated by visual auras; (5) minors in foster care; (6) inability to communicate in English; (7) pregnant women; or (8) prisoners. The exclusion of diode laser use was determined during safety testing, in which laser safety was confirmed for PDL and CO_2_ lasers but not diode lasers. Laser safety testing was performed by a third-party company to evaluate the VR headset for ocular safety. They determined that the headset was safe to use with PDL and CO_2_ lasers but did not provide protection against diode laser wavelengths. Based on the previous studies, patients aged less than 5 years were unable to respond effectively to pain measurement and other study questionnaires.

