#### Legal Guardian Data (Self-Reported when Participants are <18 y)

Before the laser procedure, all legal guardians will self-report their anxiety state using the short-form 6-item State-Trait Anxiety Inventory [36], with ratings ranging from “not at all” to “very much”. After the procedure, the legal guardian will report their perception of the participant’s pain by providing an overall pain score (NRS 0‐10) and a worst pain score (NRS 0‐10). These data will be collected at each of the 2 study visits.

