Linear mixed-effects models with participant-specific random intercepts will be fit on the composite scores to evaluate any modification of the effects of VR on pain by sex, age, and anxiety, with adjustment for baseline covariates and potential carryover effects of VR from the first to the second procedure. The following covariates will be included in the regression models: study group (VR vs control), period (second vs first procedure), study group by period interaction (test for carryover effect), age, age by study group interaction, sex, sex by study group interaction, procedural anxiety, procedural anxiety by study group interaction, race, ethnicity, State-Trait Anxiety Inventory for Children, 6-item State-Trait Anxiety Inventory, and average mYPAS scores between T0 and T1. We will include each of the 3 interaction terms in a separate regression model. Due to the limited sample size, testing the interaction may not be feasible. The study will then run the main linear models without interaction terms. The results will provide us with preliminary data to estimate the future study sample size and power. In case a significant carryover effect is detected, we will use only data from the first procedure to evaluate the VR effect using 2-sample *t* test or Wilcoxon rank sum tests (depending on the distribution of the composite scores).

All statistical analyses will follow the intention-to-treat principle, wherein participants will be analyzed according to their assigned study groups, regardless of compliance status or group switching during the study.

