## Results

This study was funded by an intramural grant from the Clinical and Translational Science Institute at NCH (grant: IFPAWRI012023) in January 2023. Enrollment started in January 2023, and data collection was completed in November 2025. The flow of participants can be seen in Figure 1. A total of 44 patients were recruited and completed the first visit, with 40 participants completing both visits. The sample was balanced, with 40 patients using the VR intervention and 40 patients participating in the control group. Reasons for not completing both visits included discontinuing laser treatment (n=3) and a lack of interest in playing the VR game (n=1). Among those who completed both visits, the age range of the sample was 6 to 21 years at recruitment, and 55% (n=22) were female. Data analysis is expected to be finished in June 2026, with a paper to follow. Future results will be disseminated through publications in peer-reviewed journals and abstracts submitted to conferences in relevant disciplines.

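### The mixed models adjust for a guardian anxiety score that is collected only for participants under 18, so as listed they would leave out the adults under complete-case fitting

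*Protocol article*

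**What the plan says.** In the Data Analysis section of the protocol article, linear mixed models with a participant random intercept are to be fitted to the composite scores. Their aim is to examine whether sex, age and anxiety modify the VR effect, adjusting for baseline covariates and possible carryover. The list is introduced by "The following covariates will be included in the regression models" and closes with "6-item State-Trait Anxiety Inventory, and average mYPAS scores between T0 and T1". No age restriction is attached to any item. The three modifier interactions go into separate models. If they prove infeasible at this sample size, the fallback is to remove interaction terms; the guardian score stays in.

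The Measures section shows whose score this is: "all legal guardians will self-report their anxiety state using the short-form 6-item State-Trait Anxiety Inventory". The subsection is headed "Legal Guardian Data (Self-Reported when Participants are <18 y".

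Under Settings and Participants, the eligible population is "dermatology patients (≥5 y) undergoing the first of a new series of laser procedures", with no upper limit. A guardian is needed only for minors: "having a legal guardian present for patients aged less than 18 years during the procedure". The Results section reports, for those who completed both visits, that "the age range of the sample was 6 to 21 years at recruitment".

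**The concern.** A mixed model copes with a missing outcome. It does not cope with a missing covariate: unless something is specified, a record without a value for any listed covariate is left out. Here the value is absent by design for adults, because no guardian report is taken, so there is no underlying value to impute.

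Three things are at stake.

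- **Age modification.** Age is one of the planned modifiers, and the exclusion is determined by age. The upper end of the observed age range would vanish from the estimate of how the VR effect changes with age.
- **Carryover.** The group-by-period term sits in the same models. A significant result switches the evaluation of the VR effect to first-procedure data only. A test that omits the adults would therefore decide how the effect is estimated for everyone.
- **Consistency.** The mixed models would rest on fewer participants than the paired comparison beside which they are reported, and the results are meant to inform the sample size and power of a later trial.

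**Working it through.** The documents give no figure of their own to reproduce here; the sample of 40 was set by budget and patient volume. The check is to follow the covariate from collection to model and then count the records that remain.

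**Step 1: who has the score.** Legal Guardian Data: guardians complete it, when the participant is under 18. Participants aged 18 or over have none.

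**Step 2: whether there are such participants.** The Results section gives a range of 6 to 21 years at recruitment among completers. The upper end of that range is a person aged 21, so at least one completer is an adult. The number, k, is not reported.

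**Step 3: whether any version of the model avoids the score.** Data Analysis lists it without condition, and the fallback removes only interactions. None does.

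**Step 4: records left.** The Results section reports data collection ending "with 40 participants completing both visits", which gives 40 × 2 = 80 visits. With k adults and complete-case fitting:

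- participants left = 40 − k
- visits left = 2 × (40 − k)
- approximate inflation of standard errors = √(40 / (40 − k))

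The values of k are assumptions. The value k = 10 is what ages spread evenly over 6 to 21 would give: 4 of the 16 whole-year ages are 18 or over, and 40 × 4/16 = 10.

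| Assumed adults k | Participants left | Visits left of 80 | Share lost | Approx. SE inflation |
|---|---|---|---|---|
| 1 | 39 | 78 | 2.5% | 1.013 |
| 2 | 38 | 76 | 5% | 1.026 |
| 4 | 36 | 72 | 10% | 1.054 |
| 6 | 34 | 68 | 15% | 1.085 |
| 8 | 32 | 64 | 20% | 1.118 |
| 10 | 30 | 60 | 25% | 1.155 |

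A random-intercept model with VR, period, age, sex and the guardian score, fitted to simulated two-period data for 40 participants with that score missing from age 18, used exactly these numbers of visits. In every case the oldest participant left was 17.

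**Step 5: two refinements.** The Results section says 44 participants completed the first visit. A mixed model can use single-visit records, so the starting base could be 80 + 4 = 84 visits; the ages of those four are not given. A participant who turns 18 between the visits could lose only the second one. Neither changes the conclusion.

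**Step 6: what is not touched.** The primary comparison of composite scores is an unadjusted paired test, and the mYPAS comparisons at each procedure use no covariates. Both keep the adults.

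**The case against.** The strongest reply is that the exclusion is inferred. The article does not say that complete-case fitting will be used, and it condenses a fuller plan. A score that does not apply to adults need not delete them: an indicator for being under 18, with the score entered only for minors, keeps every record. A statistical analysis plan that is not shown could specify this or an under-18 submodel.

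This stands as a limit on certainty. It does not remove the point, because the article is not silent: it fixes a covariate list that cannot be applied as written to the population it enrolled. The indicator would also be a step function of age, in models where age is under study.

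It is also fair that the proven loss is small. The documents establish one adult, for whom 78 of 80 visits remain. The precision argument is therefore weak; the truncated age range does not depend on k.

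Three stronger readings are tempting, and the documents do not support them.

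- A reader might infer a contradiction of the intention-to-treat statement. The article defines that principle as analysis by assigned group whatever the compliance or switching. Losing a record for want of a covariate reassigns no one.
- A reader might infer that the list is overloaded with participant-level covariates that add nothing to a within-person contrast. Both anxiety inventories, procedural anxiety and mYPAS are measured at each visit and can vary within a person, and the models also serve effect modification and adjustment.
- A reader might conclude that the model should be stripped to treatment, period and one modifier. That would delete the group-by-period term on which the plan's carryover rule relies.

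**Conclusion.** The point holds in a limited form. The guardian score is listed in every version of the mixed models but does not exist for participants aged 18 or over, of whom there is at least one among the completers. Under standard complete-case fitting, the models describe minors only, the age-by-VR estimate stops at 17 in a sample that runs to 21, and the carryover test omits the adults. The size of the loss cannot be determined from the documents: it is 2.5% of completers for one adult and 25% for an assumed ten. A reader might take this as damage to the primary result. It is not, except indirectly, through a carryover decision made on the reduced sample. The conclusion assumes that no rule elsewhere specifies how the score enters for adults.

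**What to change.** Remove the 6-item State-Trait Anxiety Inventory from the mixed models that are meant to cover all participants. Keep the group, period and group-by-period terms and the other planned covariates. If guardian anxiety is of interest, add it in a sensitivity model that is stated to be restricted to participants under 18, and report the number of participants and visits in each model. All 40 completers and the full 6 to 21 age range then stay in the main models as far as this covariate is concerned.

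The cost is a change to the covariate list and one extra model; no new data are needed. The downside is that the main model no longer adjusts for guardian anxiety. The article reports data collection as complete and analysis as in progress, so the change should be dated and recorded before these models are fitted.
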